#### Recruitment and selection of the participants

Regularly, employees were registered on their first day of sick leave by the OHS (figure 1). Since January 2002, each employee on sick leave due to mental health problems was invited to meet with a case manager of the OHS within one week. This case manager informed the employee about the study and planned a consultation with an OP in the first two weeks of sick leave. To enhance recruitment one of the researchers (DB), who was allowed to check the registration system of the OHSs, informed the OP when a potential participant would come for consultation. Each employee who consulted an OP, and was still on sick leave due to mental health problems, was then asked by the OP to participate in the study. After an employee had signed informed consent during this consultation (T0), the OP unsealed a study envelope containing the allocated treatment for the patient, and sent the signed informed consent to the researcher (DR). In the same consultation the employee received the baseline questionnaires and was asked to return this questionnaire to the researcher after completion.

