#### In- and exclusion criteria

As the guideline focuses on all kinds of mental health problems, we aimed to include employees with a broad range of mental health problems consulting their OP. Employees were included if they met the following inclusion criteria:

• Mental health problems according to the diagnosis of the OP

• Sick leave at the moment of inclusion

• Sick leave period did not start before 2002.

Exclusion criteria were the same as stated in the OP-guideline:

• Mental health symptoms that were caused by somatic illness

• Disagreement between OP and employee about the diagnosis

• Lack of confidence in the relation between OP and employee

The application of the exclusion criteria was dependent on the OPs expert judgement. To prevent selection bias, employees were not included of whom the period of sick leave started before 2002.

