	*IF patient receives effective treatment in curative sector*	PI8 = NA

**PI9**	**Advice on return to work**	

	1. Advice on return to work should be provided by OP	
	2. IF no impediments for return to work are present, THEN OP should advise full or partial return to work	
	*One or both criteria not met at each consultation?*	PI9 = 1
	*Patient already (partially) returned to work?*	PI9 = NA

**PI10**	**Timing of consultations**	

	1. First consultation should be within 3 weeks from first day of sickness absence	
	2. IF patient has not yet completely recovered, THEN next consultation should be within 4 weeks from previous consultation	
	*Criterion 1 not met at first consultation OR criterion 2 not met at consultation 2 or 3?*	PI10 = 1

Additionally, this audit gave us information about treatment compliance by the OP (guideline adherence) in both groups. In this way contamination between the study groups was studied as well. Adherence in the intervention group was considered compliant if there was adequate adherence. Guideline adherence in the control group was considered compliant if there was deviant adherence.

The performance indicators will be assessed on their criteria by three independent researchers, resulting in a dichotomised score on guideline adherence for each employee (adequate versus deviant).

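### PI10 counts the timing of the first consultation, which is settled before allocation, in the score read as OP compliance with the allocated arm

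*Protocol article*

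**What the plan says.** **Order of events.** Under Recruitment and selection of the participants, an OHS case manager meets the employee and "planned a consultation with an OP in the first two weeks of sick leave". Allocation comes later, in the OP consultation: "After an employee had signed informed consent during this consultation (T0), the OP unsealed a study envelope containing the allocated treatment for the patient". Inclusion requires "Mental health problems according to the diagnosis of the OP" and current sick leave. The only limit on when the leave began is "Sick leave period did not start before 2002", so no maximum duration at inclusion is set.

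**The indicator.** In Table 5 (Guideline adherence by the OP), PI10 has two criteria. The first is "First consultation should be within 3 weeks from first day of sickness absence". The second concerns the interval between later consultations. PI10 scores 1 under the condition "Criterion 1 not met at first consultation OR criterion 2 not met at consultation 2 or 3", so a failure of criterion 1 is enough.

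**Use of the score.** Adherence is deviant when at least three of the ten indicators score 1. The section adds that "this audit gave us information about treatment compliance by the OP (guideline adherence) in both groups", and that contamination is studied in the same way. An intervention patient counts as compliant when adherence is adequate, a control patient when it is deviant. The Discussion (Contamination between study groups) rests the per-protocol analyses on this adherence measure, and Data analysis compares per-protocol with intention-to-treat results.

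**The concern.** A measure of compliance with an allocated arm should reflect what the OP did once the arm was known. Criterion 1 reflects scheduling before that point. Because the score is read in opposite directions in the two arms, the same late first visit counts against the OP's use of the guideline in one arm and as delivery of control care in the other, with no difference in conduct after allocation.

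This matters for two reasons. Compliance and contamination rates absorb something allocation cannot change. The per-protocol sets also become unbalanced in pre-randomisation delay: late-seen patients tend to leave the intervention set and join the control set. Full return to work is counted from the first day of sick leave, and participants must still be on leave at inclusion, so anyone failing criterion 1 already has more than 21 days in the outcome. The imbalance tends to lengthen control durations relative to intervention durations, which favours the guideline without any treatment effect.

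**Working it through.** The article states no adherence, compliance or late-visit rate, so there is no figure of its own to reproduce. The check has a logical part and a sizing part.

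**1. Is criterion 1 settled before allocation?** The first OP consultation is either the T0 consultation or an earlier one. The envelope is opened during T0, after consent. In both cases the date of the first consultation is fixed before the arm is known. Nothing restricts the audit to conduct after allocation; Table 1 marks guideline adherence at T0 as well.

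**2. When does PI10 change the classification?** With a cut-off of three, only when exactly two of the other nine indicators score 1. Assume these fail independently with probability q:

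P(exactly 2 of 9) = 36 × q² × (1 − q)⁷

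| q (assumed) | P(exactly 2 of 9) | × (1 − q), if criterion 2 also fails at rate q |
|---|---|---|
| 0.2 | 0.302 | 0.242 |
| 0.3 | 0.267 | 0.187 |
| 0.4 | 0.161 | 0.097 |

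So criterion 1 reclassifies about 16–30% of late-seen patients if they meet criterion 2. It reclassifies about 10–24% if criterion 2 fails as often as the other indicators, because PI10 would then sometimes be 1 anyway.

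**3. Shift in compliance rates.** Let r be the share seen after three weeks, the same in both arms, and let criterion 2 fail at rate q. Then shift = r × (1 − q) × P(exactly 2 of 9). With q = 0.2 in the intervention arm and 0.4 in the control arm:

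| r (assumed) | Intervention compliant | Control compliant |
|---|---|---|
| 0 (same as dropping criterion 1) | 67.8% | 83.3% |
| 10% | 65.4% | 84.2% |
| 20% | 62.9% | 85.2% |
| 30% | 60.5% | 86.2% |

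The pairs (0.15, 0.35) and (0.25, 0.25) were also run. Over all three pairs with r at 10–30%, intervention compliance falls by about 2–7 points and control compliance rises by about 1–7 points.

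**4. Composition of the compliant sets.** Take q = 0.3 in both arms, r = 20% and criterion 2 always met. From Bin(9, 0.3), P(<2) = 0.196 and P(<3) = 0.463.

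- Late share of compliant intervention patients: 0.2 × 0.196 / (0.2 × 0.196 + 0.8 × 0.463) = 0.096.
- Late share of compliant control patients: 0.2 × 0.804 / (0.2 × 0.804 + 0.8 × 0.537) = 0.272.

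Without criterion 1 both would be 20%. If criterion 2 also fails at 0.3, a patient seen in time is adequate with probability 0.7 × 0.463 + 0.3 × 0.196 = 0.383, and the shares become 0.039/(0.039 + 0.8 × 0.383) ≈ 11% and 0.161/(0.161 + 0.8 × 0.617) ≈ 25%. At r = 2% with criterion 2 always met, they are about 0.9% and 3.0%.

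**The case against.** The strongest defence is that criterion 1 may seldom fail. Consultations are planned for the first two weeks and the criterion allows three. That stands as a limit on size. It does not remove the point, because two weeks is a planning target and no maximum sick-leave duration is set.

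A second defence is that little depends on the score. The main analyses are intention-to-treat. The Compliance section adds referral proportions to the DGZ psychologist, a compliance measure without this flaw. Data analysis enters sick leave up to inclusion as a covariate in the return-to-work model, which may absorb part of the delay. All of this stands. However, the covariate text does not name the per-protocol analysis, and a covariate cannot repair compliance and contamination rates or unadjusted Kaplan–Meier curves.

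A reader might go further and infer that PI1–PI5 are also fixed before allocation, since their windows open at the first consultation and a diagnosis is needed for inclusion. The article does not support that. These indicators score 1 only if criteria remain unmet within two consultations, so when T0 is the first visit the window covers the rest of T0 and all of the second visit. Inclusion requires a diagnosis of mental health problems, not notes on work-related causes, functional limitations or curative care. The windows of PI6–PI9 open at the same point, so PI1–PI5 are not a special case. Scoring PI1–PI5 only from the second consultation would do harm: an OP who documented everything correctly at T0 and did not repeat it could be marked deviant on up to five indicators.

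**Conclusion.** The point holds for PI10 criterion 1. It scores an interval that allocation cannot affect, inside a total read in opposite directions as compliance in the two arms and used for contamination and the per-protocol comparison. The resulting artefact has a direction: it moves late-seen patients towards the control compliant set.

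Its size is conditional. It acts only on late-seen patients with exactly two other deviant indicators who have not also failed criterion 2. Under the assumed rates, compliance figures shift by about 1–7 points when 10–30% are seen late, and not at all when everyone is seen within three weeks. These results assume independent indicators, all ten applicable, and the same late share in both arms. The article supplies none of the rates, so the figures show what could happen and do not estimate what did.

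A reader might conclude that the intention-to-treat result is biased or that the reported compliance must be wrong. Neither follows: the former does not use the score, and the latter depends on an unknown late share.

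**What to change.** For the compliance classification, the contamination measure and the per-protocol sets, score PI10 on criterion 2 only. This keeps ten indicators and the cut-off of three. Report the interval from first sick day to first consultation by arm as a baseline characteristic. Keep the full ten-indicator score, with both PI10 criteria, as a description of guideline adherence.

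Leave the scoring of PI1–PI9 as it is, and add a sentence noting that their windows open at the T0 consultation and may include entries made before allocation.

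The cost is a change of wording in the scoring rule. The indicators are already audited from the OHS medical files, so no new data collection is needed. The drawback is that the compliance score departs slightly from the validated indicator set.

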#### Guideline adherence by the OP

The aim of this study is to examine the effectiveness of the management by Dutch OPs, under the expectation that (training in) the guideline will lead to additional skills for the OP and consequently to positive outcomes. To explore our hypothesis that the guideline leads to additional skills and outcomes, we examined the performance by the OP according to the guideline (guideline adherence). Guideline adherence by the OP was checked by means of an audit of the medical files. Guideline adherence was defined as the total score on ten validated performance indicators for the treatment of each participant by the OP (table 5)[11,18,36]. For each performance indicator, we used validated criteria. If a criterion was not met, the case was assigned 1 for that performance indicator. If all applicable criteria for a performance indicator were met, the resulting score was 0 for that case. The medical files of all the participants were assessed on if they met the criteria of the different indicators (0=adequate care; 1=deviant care). In this way an average performance rate was obtained for each performance indicator. Furthermore, a total score of all performance indicators was calculated (guideline adherence). Guideline adherence was dichotomized into adequate adherence and deviant adherence. Adherence was considered deviant if three or more performance indicators were assigned a score of 1, and adequate if less than three performance indicators had a score of 1.

**Table 5 T5:** Performance indicators guideline adherence and their criteria 1 = deviant care, NA = Not applicable

**PI 1**	**Assessment of symptoms**	**Score**
Criteria:	1. Presence or absence of essential symptoms of anxiety disorder and depressive disorder should be noted in file	
	2. Presence or absence of distress symptoms (fatigue, concentration problems, sleeping problems, and emotional reactivity) should be noted in file	
	*One or both criteria not met within 2 consultations?*	PI1 = 1

**PI 2**	**Correct diagnosis**	

Criteria:	1. Diagnosis should be noted in file	
	2. Diagnosis should be correct:	
	- IF adjustment disorder: at least one psychological distress symptom should be noted in file	
	- IF depressive disorder: at least one essential symptom AND five depressive symptoms should be noted in file	
	- IF anxiety disorder: at least one anxiety disorder should be noted in file	
	3. Diagnosis should not be missed if criteria above apply	

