	*One or more criteria not met within 2 consultations?*	PI2 = 1

**PI 3**	**Evaluation curative care**	

Criteria:	1. Treatment in the curative sector, or its absence, should be noted in file	
	2. IF patient receives treatment, THEN the OP should evaluate whether this treatment is effective	
	*One or both criteria not met within 2 consultations?*	PI3 = 1

**PI 4**	**Assessment work-related causes**	

Criteria:	1. the work-related causes, or their absence, should be stated in file	
	*One or both criteria not met within 2 consultations?*	PI4 = 1

**PI 5**	**Evaluation of work disabilities**	

Criteria:	1. Functional limitations in home or work environment, or their absence, should be stated in file.	
	2. Work activities of patient should be noted by OP	
	3. OP should assess whether patient is limited in his work functioning	
	4. IF patient has work limitations, THEN OP should assess other impediments for return to work (such as problems in home situation or with supervisor)	
	One or both criteria not met within 2 consultations?	PI5 = 1

**PI6**	**Interventions targeted at individual**	

	1. Intervention aimed at the individual should be noted or be referred - IF adjustment disorder, THEN OP should start interventions OR should refer patient to psychologist/social worker/general practitioner OR should consult with practitioner giving current treatment - IF anxiety disorder OR depression OR other psychiatric disorder, THEN OP should refer patient to psychologist/social worker/general practitioner OR should consult with practitioner giving current treatment	
	*Criterion not met within 3 consultations?*	PI6 = 1

**PI7**	**Interventions targeted at organisation**	

	IF work is a causal, eliciting or maintaining factor in the mental health problem, THEN OP should intervene in the work organisation (confer with supervisor/personnel officer)	
	*Criterion not met within 3 consultations?*	PI7 = 1
	*IF work is neither causal, eliciting nor maintaining factor in mental health problem*	PI7 = NA

**PI8**	**Interventions targeted at providers of care in curative sector**	

	1. IF treatment in curative sector is lacking and deemed necessary, THEN OP should start interventions targeted at the individual OR refer patient to psychologist/social worker/general practitioner	
	2. IF treatment in curative sector is not effective, THEN OP should consult with practitioner giving current treatment	
	*One or both criteria not met within 3 consultations?*	PI8 = 1

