### Study population: sample size and power analysis

In order to detect a relevant difference in survival analysis on our primary outcome return to work, nQuery Advisor [37] was used to calculate the sample size. Proportions used to determine the sample size needed, were analysed from sick leave data of the police constabularies in 1999. In 1999, 286 employees were registered as being on sick leave due to mental health problems, which was 6.6 % of the total sick leave registrations. Their duration of sick leave in 1999 was 35.5 % of the total volume of sick leave, with an average of three months per case. With a power of 90%, at a 0.05 level, a two-sided log-rank test for equality of survival curves was done, assuming a difference between the intervention and control group proportion still on sick leave after one year of 0.25. This test indicated that a sample size was needed of 107 in each group. Assuming a dropout rate of 20%, inclusion of a total of 268 patients was necessary to statistically detect a clinically relevant difference.

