To assess whether protocol deviations will cause bias, the results of the intention-to-treat analyses will be compared to per-protocol analyses. A process evaluation will be done, based on the assessment of guideline adherence by means of performance indicators [18]. For each performance indicator potential effects on our primary outcomes will be measured.

Indirect costs can be calculated using the friction cost approach (friction period 122 days) and the human capital approach, based on income as provided by the employer or as derived from function, age and gender [30]. Bootstrapping will be used for pair wise comparison of the mean groups to calculate mean differences and confidence intervals in costs and cost-effectiveness ratios for all interventions. All these analyses will be conducted in SPSS 14.0, Excel and, if necessary, in Strata.

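### The per-protocol comparison selects the two arms in opposite directions on an adherence score linked to return to work, so it cannot show whether protocol deviations biased the intention-to-treat result

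*Protocol article*

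**What the plan says.** Under *Guideline adherence by the OP*, medical files are audited on ten performance indicators. Each scores 1 if a criterion is not met and 0 if all applicable criteria are met. The total is then cut: "Adherence was considered deviant if three or more performance indicators were assigned a score of 1"; fewer than three is adequate. The cut-off is not rescaled when an indicator is not applicable (NA).

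The same section defines compliance. Intervention patients are compliant if adherence is adequate. For controls the rule is reversed: "Guideline adherence in the control group was considered compliant if there was deviant adherence".

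Table 5 gives the scoring rules. PI9 (advice on return to work) becomes NA on the condition "Patient already (partially) returned to work". The second criterion of PI10 (interval to the next consultation) applies only to patients not yet fully recovered. PI1 to PI5 are judged over two consultations and PI6 to PI8 over three. For an adjustment disorder, PI6 is met if the "OP should start interventions OR should refer patient to psychologist/social worker/general practitioner".

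Under *Data analysis*, all analyses follow intention to treat. To judge bias from protocol deviations, "the results of the intention-to-treat analyses will be compared to per-protocol analyses". *Contamination between study groups*, in the Discussion, bases the per-protocol analyses on guideline adherence by the occupational physician (OP).

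**The concern.** A per-protocol comparison is already weaker than ITT because it selects on something that happens after randomisation. Here the selection is opposite in the two arms: low scorers are kept in the intervention arm and high scorers in the control arm. If the score is related to time to return to work for any reason other than treatment, the two retained groups differ in prognosis even when treatment does nothing.

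The relation is written into the scoring. A patient who goes back early can have PI9 set to NA, and NA counts like a met indicator against a fixed cut-off of three. The same patient escapes the second criterion of PI10.

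Contamination is the weakness the authors themselves acknowledge, since the same trained OPs treat both arms. The per-protocol comparison is the stated check on bias from deviations. If it can differ from ITT in either direction with no treatment effect, a gap between the two does not reveal contamination, and agreement does not rule it out.

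**Working it through.** **What the document supplies.** It gives the two compliance rules, the cut-off of three, the NA rules and consultation windows, a mean sick-leave duration of three months, one year of follow-up, and 107 patients per group. The stated total agrees with 107: 2 × 107 / 0.8 = 267.5, rounded up to 268. It is used here only as a trial size. The article gives no indicator failure rates, so those below are assumptions.

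**Which indicators depend on the outcome.**
- PI9: NA after partial or full return.
- PI10, criterion 2: only for those not recovered.
- PI10, criterion 1: fails if the first consultation is more than three weeks into sick leave. The outcome counts from the first day of sick leave, and patients are still off work at inclusion. If the inclusion consultation is the first, failing means an outcome above 21 days before allocation is known. The simulation below leaves this link out.
- PI6 has no NA rule. PI7 is NA only if work plays no part in the problem, and PI8 only if curative treatment is effective. None of these switches off on return to work.

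**Simple count.** Assume half of each arm recovers fast, each applicable indicator fails with probability 0.3, ten apply to slow recoverers, and nine to fast recoverers (PI9 removed).
- P(at least 3 of 10) = 0.617, so 0.383 of slow recoverers are adequate.
- P(at least 3 of 9) = 0.537, so 0.463 of fast recoverers are adequate.
- Fast share kept in the intervention arm: 0.463 / (0.463 + 0.383) = 54.7%.
- Fast share kept in the control arm: 0.537 / (0.537 + 0.617) = 46.5%.
- Gap with no treatment effect: about 8 percentage points.

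**Simulation with no treatment effect and no effect of adherence.** Time to return is exponential with mean 91 days (true median 91 × ln 2 = 63). Consultations fall on days 0, 28 and 56 while the patient is off work. The ten indicators are scored by Table 5, with failure rates of 15% to 35% and late follow-up consultations in 20% to 50%. Bias comes from 400,000 patients per arm; false-positive rates come from trials of 107 per arm before selection. The ITT hazard ratio is 1.00 throughout. Values above 1 favour the intervention.

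| Treatment of the 2- and 3-consultation windows | Per-protocol HR | Falsely significant |
|---|---|---|
| PI1–PI8 unrelated to number of consultations; only PI9 and PI10 linked to return | 1.16 to 1.34 | 8% to 29%, for the intervention |
| Unfinished windows not scored (failure rate 25%) | about 2.0 | 96%, for the intervention |
| Unmet criteria scored 1, with an independent chance to meet them at each consultation | 0.56 to 0.75 | 11% to 83%, almost all against the intervention |

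As an example, take 25% failure and 35% late follow-up. The retained medians are 51 days (intervention) and 74 (control) in the first row, but 88 and 49 in the third.

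Between rows one and three the sign changes. Suppose a two-consultation indicator fails in 25% by the second consultation. The hazard ratio is 1.02 if 32.5% had failed at the first consultation, and 0.89 if 37.5% had.

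Keeping adequate patients in both arms returns 1.00, so the opposite rules are the source. That is a diagnostic rather than a remedy, since allocation is meant to change adherence.

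**Control compliance against control care.** *Usual care* and *Contamination* describe minimal OP involvement with ready referral to a psychologist. PI6 scores that referral as met. PI8 does so too where treatment is lacking and needed, and becomes NA once curative treatment works. Delivering control care as designed thus moves a control patient towards non-compliant. PI1 to PI5 rest largely on what is noted in the file, so thin records count as delivering usual care. This part needs no assumed rates.

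**The case against.** **The rule is a sensible contamination check.** A control patient whose care looks like guideline care is the contaminated case. As a description of each arm that is reasonable, and the audit is planned for both arms. It does not carry over to choosing whom to compare.

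**The per-protocol set is not spelled out.** *Data analysis* does not define it, and *Compliance* names a second measure, referrals to the psychologist. The link to the reversed rule is therefore an inference. It is a close one: the Discussion ties the per-protocol analyses to guideline adherence, and no cut-off is given for referrals.

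**It is a supporting analysis.** ITT governs the main results. This stands and limits the weight of the point.

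**The bias need not favour the intervention.** A reader might infer that the rule favours the intervention by construction, because fast recoverers drift to adequate. Table 5 does not support that. Its consultation windows are periods in which to meet a criterion, and an unmet criterion scores 1, so early returners can look more deviant. No rule covers a window cut short by return to work.

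**A gap as large as the planned effect is not supported either.** With seven indicators for fast recoverers and ten for slow, the simple count gives 62.8% against 36.4%, about 26 points, which invites comparison with the planned 0.25. Return to work removes at most PI9 as a whole indicator, which gives about 8 points. The planned 0.25 is a difference in the proportion still on sick leave at one year, which is a different quantity.

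**Conclusion.** The point holds in this form: opposite selection on a post-randomisation score partly tied to return to work makes the per-protocol comparison unable to show whether protocol deviations biased the ITT result. PI9 and PI10 push towards the intervention. The net direction and size are not fixed by the document, because they depend on how unfinished windows are scored. Across the settings examined the null hazard ratio ranged from 0.56 to about 2.0. Those figures rest on assumed failure rates, consultation times and exponential durations; the existence of the problem does not. The mis-measurement of control compliance follows from the text alone.

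That the ITT result would be wrongly explained away as contamination is a possible consequence, not something the document shows. The primary ITT analysis is untouched.

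**What to change.** - Drop the rule that deviant adherence makes a control patient compliant, and do not use that set to judge bias in the ITT result.
- Define compliance in each arm by the care that arm was meant to receive. For controls, use the extent of OP involvement, with referral not counted as non-compliance.
- Assess it in a fixed early window that does not depend on return to work, such as the inclusion consultation. Leave out PI9 and PI10, and score the proportion of applicable indicators.
- Use the already planned adherence and referral proportions by arm as the measure of contamination.
- If an effect of adherence is wanted, give a complier estimate with allocation as instrument, as a sensitivity analysis for the whole treatment package. State that allocation also changes the advice on and funding of referral, so the exclusion restriction for guideline adherence alone is doubtful.

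The cost is re-scoring audit data already planned for collection, plus some rewording. The complier estimate will have wider intervals. An early window says nothing about later care, and part of the inclusion consultation precedes opening of the envelope.
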